#### Accommodation procedures

The accommodation period for all three FRO configurations will include a gradual increase in the length of time the FRO is worn each day, in order to minimise the risk of adverse events. Patients will be contacted one week after setting each new FRO configuration, to check for adverse events such as pain, discomfort, or pressure sores. If the patient has no complaints, the accommodation period will continue until the next visit (four to eight weeks later). When adverse events are reported, the investigator will identify the causes and make an appropriate decision according to protocol. The accommodation period will not start until all complaints are resolved.

#### Optimal AFO selection procedure

Following a standard procedure, evaluation of FRO efficacy of the three configurations (T1_k1_, T1_K2_ and T1_K3_) will lead to selection of the subject’s optimal FRO configuration (Figure
2). Since clinical assessment of FRO effectiveness in children walking with excessive knee flexion is mainly based on knee kinematics in stance, the minimum amount of knee flexion (i.e. peak knee extension) in the single support phase will be the main discriminating parameter. The configuration that results in smallest peak knee flexion will be selected as the subject’s optimal FRO. Differences of less than 5º will be considered equal, since this angle lies within the variability of 3D gait analysis
[46]. Should minimum knee flexion in single support be unable to discriminate between the remaining configurations, walking energy cost (expressed as net non-dimensional energy cost relative to speed-matched control cost (NN_EC_%SMC_)
[47,48] will be decisive. In this situation, the FRO that results in the lowest NN_EC_%SMC_ will be selected as the subject’s optimal FRO. 

**Figure 2 F2:**
[figure not shown]
**Flowchart of the optimal FRO stiffness selection procedure. **After sorting the different stiffness configurations based on peak knee extension angle in single support (KE-K_x_), absolute differences in peak KE will be calculated. KE-K_2_ and/or KE-K_3_ will be excluded if this difference is more than five degrees. Otherwise, the remaining configurations will be sorted by net non-dimensional walking energy cost (NNC-K_x_) (this can be either two or three remaining configurations). The stiffness that results in the lowest walking energy cost will be selected as the subject’s optimal FRO. K_1,_ K_2_ and K_3_ = rigid, stiff, or flexible FRO stiffness configurations; K_OPT_ = subject’s optimal FRO stiffness; KE = knee extension angle; KE-K_x_ = stiffness sorted by KE; NN_cost_%SMC_ = net non-dimensional walking energy cost relative to speed matched controls; NNC-K_x_ = stiffness sorted by NN_cost_%SMC_; SS = single support.

### Outcome measures

Outcome measures for this study are categorised in accordance with the ICF
[34] and cover the components ‘body functions and structures’ and ‘activities and participation’, as well as personal and environmental factors. An overview of all outcome measures is presented in Table
2. 

**Table 2 T2:** Overview of tests performed at different measurement moments

		**T0**	**T1**_**k**_*****	**T2**_**kopt**_
**Primary study parameters**				
*Activities and participation*	ECWT	x	x	x
**Secondary study parameters**				
*Body functions and structures*	3D-gait analysis	x	x	x
*Activities and participation*	SAM***	x	x	x
	CAPE***	x		x
**Effect modifiers**				
*Body functions and structures*	Physical fitness test	x		
*Environmental and personal factors*	Physical examination**	x		
	Gait pattern	x		
	Intake questionnaire	x		
	BSS	x		
	FMS	x	x	x
	FAQ	x	x	x
	GMFCS	x		
***Other outcomes***				
	GAS	x		x
	FRO properties	x	x	x
	Motivation diary	x	x	x
	@ monitor		x	x
	Satisfaction	x	x	x

*T1_k_ will be repeated for each FRO-configuration: rigid, stiff and flexible.

** The physical examination includes passive Range of Motion, selective motor control and gross motor function tests.

***SAM and CAPE data will be assessed in the week prior to the ticked measurement moment.

BSS=’Bronnen van Steun en Spanning’; CAPE=Children’s Assessment of Participation and Enjoyment; ECWT=Energy Cost of Walking Test; FAQ=Functional Assessment Questionnaire; FMS=Functional Mobility Scale; FRO=Floor Reaction Orthosis; GAS=Goal Attainment Scaling; GMFCS=Gross Motor Function Classification System; SAM=StepWatch3^TM^ Activity Monitor.

#### Primary outcome

Our primary outcome measure is walking energy cost, which will be measured during a 6-minute walking test on an indoor oval track. Subjects will be asked to walk at a self-preferred comfortable speed, during which oxygen uptake and carbon dioxide production will be measured using the accurate and reliable Metamax 3B portable gas analysis system (Cortex Biophysik, Leipzig, Germany). Calculations will be based on measurements during a steady state of walking, defined as a period of at least one minute in which fluctuations in walking speed, oxygen uptake and carbon dioxide production show the least change
[48].

Mean steady-state breath-by-breath oxygen uptake values and respiratory exchange ratios will be computed. Using these values, gross and net energy consumption will be calculated and normalised according to the net non-dimensional (NN) scheme of Schwartz et al.
[48]. The primary outcome measures will be expressed as net energy cost and as NN energy cost as a percentage of speed-matched controls (NN_EC_%SMC_). Furthermore, non-dimensional walking speed (N_speed) (a secondary outcome measure) will be calculated.

EC measurements in children with CP are sufficiently sensitive, as shown by Brehm et al.
[49]. The NN normalisation scheme of Schwartz et al. is suggested to be the preferred method for reporting oxygen consumption data for subjects who have not reached their full stature, since it is largely independent of mass, height and age
[48].

#### Secondary outcome

Secondary outcome measures include daily activity, gait biomechanics, walking speed (N_speed) and diversity, intensity and enjoyment of participation (assessed with the Children’s Assessment of Participation and Enjoyment [CAPE]). Two of these outcome measures (daily activity and gait biomechanics) are further explained below.

##### Daily activity

Daily activity will be measured for one week with a StepWatch3™ Activity Monitor 3.0 (SAM) (Cyma Corporation Seattle, WA, USA), which is an ankle worn accelerometer that measures the average amount of steps per minute over a broad spectrum of cadences. The SAM will be attached to the ankle of the dominant leg. Subjects will be instructed not to remove the SAM at any time, except when taking a bath or shower or when swimming. For adequate interpretation of the data, subjects will be asked to keep a diary of their activity program during each day of the week.

Daily activity will be determined as 1) average total steps per day, 2) percentage of time children were active, 3) percentage of time children were inactive, 4) ratio of medium to low activity levels and 5) percentage of time children show high activity levels. A calibrated SAM has been shown to be an accurate tool for recording daily steps in children with CP
[50,51].

##### Gait biomechanics

Joint kinematics will be assessed in the laboratory, using a three-dimensional (3D) motion analysis system (OptoTrak, Northern Digital, Waterloo, Canada), while the subject walks on a 10m walkway at a self-preferred comfortable speed. Marker clusters will be attached to the feet, shanks, thighs, pelvis and trunk. To determine anatomical coordinate systems, anatomical landmarks will be palpated according to Cappozzo et al.
[52]. Joint kinetics will be calculated by assessment of the ground reaction force, using an integrated force plate (AMTI OR6-5-1000, Watertown, MA, USA).

At baseline, all subjects will be measured walking bare foot and with shoes only. An additional condition (old FRO-footwear combination) will be included for children who have (suitable) old orthoses. Follow-up recordings will be made while walking with the new FRO-footwear combination. Six trials, with the subject stepping on the force plate, will be completed for each condition (i.e. three trials for each leg). Data on joint kinematics, and kinetics around the hip, knee and ankle will be averaged. Spatio-temporal parameters, such as step length [m], step width [m] and cadence [steps⋅min^-1^] will also be calculated.

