**Figure 1 F1:**
[figure not shown]
**Schematic representation of the study design. **Following baseline measurements (T0), the subject’s will be prescribed an interventional FRO. The stiffness of this FRO will be varied (rigid, stiff and flexible) and the order of FRO stiffness will be block randomised. Accommodation time for each stiffness will last 4–8 weeks, after which effects will be evaluated (T1_K1_, T1_K2_, and T1_K3_). Following these evaluations, an optimal FRO for the subject will be selected. Follow-up measurements (T2_Kopt_) will be carried out at 12–20 weeks. B=Block; FRO= Floor Reaction Orthosis; K=AFO stiffness; K_1_, K_2_, and K_3_ represent either rigid, stiff or flexible stiffness configurations.

Following completion of study enrolment, baseline measurements (T0) will be performed barefoot, with shoes only and with the subject’s current orthosis (if applicable). Stiffness (K) of the new FRO will be varied into three configurations: rigid, stiff, and flexible. A balanced block randomisation will be applied for six possible sequences of stiffness configurations, to ensure that the same number of patients is allocated to each sequence. Every configuration will be worn for an accommodation period of four to eight weeks, after which FRO efficacy will be evaluated (T1_k1_,T1_K2_ and T1_K3_). An analysis of the evaluation of all FRO configurations will allow the selection of the stiffness with the maximal benefit for a particular subject, referred to as the subject’s optimal FRO (the selection procedure is explained further below). Following this selection, the optimal FRO will be worn for twelve to twenty weeks, after which the follow-up measurements (T2_Kopt_) will be taken.

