#### Evaluation of FRO efficacy

Evaluation of the efficacy of a subject’s optimal FRO will be based on analyses of pre/post-intervention differences in primary and secondary outcome measures. The pre-intervention (control) condition will be for shoes only. Mean data for these measurements (assessed at T0) will be compared to follow-up measurements (T2_Kopt_), using paired sample t-tests.

To identify working mechanisms, multivariate linear regression analyses will be applied to investigate which of the changes in gait biomechanics are associated with changes in walking energy cost (model 1) and daily activity (model 2). First, a univariate regression analysis (ANOVA) will be performed to determine which factors are significantly associated with changes in the biomechanics of gait (p≤0.1), followed by the analysis of significant factors (p≤.05) in a multivariate regression analysis model.

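### Step length and step width in metres and cadence in steps/min enter an uncontrolled T0–T2 comparison in growing children, so growth alone can lengthen the raw step and be credited to the FRO

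*Protocol article*

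**What the plan says.** Under Gait biomechanics, the protocol article names "Spatio-temporal parameters, such as step length [m], step width [m] and cadence" as quantities to be calculated. Lengths are in metres and cadence in steps per minute. No division by height or leg length is stated there or elsewhere.

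The Secondary outcome section makes gait biomechanics a secondary outcome: "Secondary outcome measures include daily activity, gait biomechanics, walking speed (N_speed"). Under Evaluation of FRO efficacy, shoes-only data from T0 "will be compared to follow-up measurements (T2_Kopt_), using paired sample t-tests". The same section plans regressions "to investigate which of the changes in gait biomechanics are associated with changes in walking energy cost (model 1) and daily activity (model 2").

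The timing is in the text with Figure 1. "Every configuration will be worn for an accommodation period of four to eight weeks", there are three configurations, and then "the optimal FRO will be worn for twelve to twenty weeks" before T2. The inclusion criteria set an age of 6–14 years.

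The Primary outcome section normalises energy cost by a net non-dimensional scheme, described as "the preferred method for reporting oxygen consumption data for subjects who have not reached their full stature". It also makes walking speed non-dimensional. Energy cost is reported both as net energy cost and in non-dimensional form relative to speed-matched controls.

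**The concern.** Walking speed is step length multiplied by cadence. The article scales the product for body size but gives its two components in raw units. A child whose non-dimensional speed has not changed, but who has grown, will tend to take a longer step in metres.

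Each child is compared with him- or herself many weeks earlier, with no control group followed over the same time. The paired test therefore cannot separate leg growth from the effect of the orthosis. For step length the bias has one direction, towards a longer step at T2, which a reader would take as a benefit.

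At stake is a false or inflated secondary finding on step length. Raw cadence and step width would also shift with growth, but the article names neither direction as an improvement. For those two the result would be hard to interpret rather than falsely favourable.

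**Working it through.** **The plan's own figure.** The article gives no figure for spatio-temporal parameters. Its only design figure is 29 evaluable children for energy cost (Sample size). The two-means formula reproduces it: 2 × (1.960 + 0.842)² × 1.70² / 1.26² = 28.6, rounded up to 29. It is used below only as the number of pairs.

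**Interval from T0 to T2 (Figure 1 text).**
- Shortest: 3 × 4 + 12 = 24 weeks.
- Longest from the stated periods: 3 × 8 + 20 = 44 weeks.

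Both are minimum values. Time to make the FRO is not counted. Under Accommodation procedures, a period does not start until complaints have been resolved.

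**Assumptions, none of them in the article.** Growth 5–6 cm/year; height 125–135 cm; step length 45 cm and proportional to height; SD of the T0–T2 change in step length 4–6 cm; true FRO effect on step length zero.

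**Shift in step length from growth alone.** Shift = 45 cm × (growth rate × weeks / 52) / height.
- Low end: 5 × 24/52 = 2.31 cm of growth; 2.31/135 = 1.7%; 45 × 0.0171 = 0.77 cm.
- High end: 6 × 44/52 = 5.08 cm of growth; 5.08/125 = 4.1%; 45 × 0.0406 = 1.83 cm.

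**Chance that the two-sided 5% paired t-test rejects.** The noncentrality is shift × √29 / SD, with 28 degrees of freedom and critical value 2.048.

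| Case | Shift (cm) | SD (cm) | Noncentrality | Rejects |
|---|---|---|---|---|
| Low end | 0.77 | 6 | 0.69 | 10% |
| 5.5 cm/year, 130 cm, 24 weeks | 0.88 | 5 | 0.95 | 15% |
| 5.5 cm/year, 130 cm, 34 weeks | 1.24 | 5 | 1.34 | 25% |
| 5.5 cm/year, 130 cm, 44 weeks | 1.61 | 5 | 1.74 | 39% |
| High end | 1.83 | 4 | 2.46 | 66% |

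Every case exceeds the nominal 5%. If step length is proportional to body length, dividing by body length at the same visit removes the shift and the rate returns to 5%.

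**Sensitivity.** With wider assumptions (4–7 cm/year, height 115–155 cm, 50 cm step, SD 3–7 cm) the rate runs from 7% to 99%. At 5 cm/year, 135 cm and SD 5 cm it is 14% at 24 weeks and 37% at 44 weeks.

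**Cadence.** If cadence varies with one over the square root of body length, growth of 1.7–4.1% changes it by 1.0171^(−0.5) − 1 = −0.8% to 1.0406^(−0.5) − 1 = −2.0%.

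**Mechanism regressions.** These use differences between children in the size of change; a growth shift common to all goes into the intercept. If the growth contribution varied uniformly from 0.8 to 1.8 cm, its SD would be 1.0/√12 = 0.29 cm. Against an SD of change of 4–6 cm, that is (0.29/6)² to (0.29/4)², or 0.2–0.5% of the predictor's variance. Even if growth fully determined the change in energy cost, the induced correlation would be only about 0.05–0.07.

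**The case against.** **The units may be units of calculation only.** The article says these parameters will be calculated and gives their units. The analysis section does not name them one by one. A full protocol or SAP, not shown, might scale them before testing. That possibility is fair, but the published text states raw units for these parameters and a scaled form for speed. Anyone who follows it as written runs a biased comparison.

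**The parameters are minor.** Speed is the only spatio-temporal measure named in the Secondary outcome section, and it is scaled. Step length, step width and cadence come in a closing sentence after kinematics and kinetics. This stands, and it limits the weight of the point.

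**The size rests on outside assumptions.** This also stands. The direction for step length follows from growth and the stated interval, but the rejection rates do not come from the article. The top of the range needs the fastest assumed growth, longest interval, lowest height and smallest SD together.

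**Stronger readings that the article does not support.** A reader might infer that growth creates a false mechanism in models 1 and 2. The variance calculation shows little room for that, and the article describes non-dimensional energy cost as largely independent of mass, height and age. A weak link through net energy cost, which is not non-dimensional, remains possible. A reader might also infer that all three parameters will falsely appear improved; that is clear only for step length. Nor is there a clean split between scaled and unscaled outcomes, because net energy cost is itself one of the two primary expressions.

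**Conclusion.** The point holds for the T0–T2 paired tests on the spatio-temporal parameters, and mainly for step length. The stated units, the age range and the uncontrolled interval of at least 24–44 weeks together mean that growth alone lengthens the raw step and can be credited to the FRO. This is out of step with the article's own non-dimensional walking speed.

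On the assumed values, the shift is about 0.8–1.8 cm (1.7–4.1%) and the false-positive rate is about 10–66%, or 15–40% at mid values, instead of 5%. These rates are illustrations and depend on growth, height, step length, proportional scaling and SD of change, none of which the article gives.

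The primary comparison is not affected by this point, and the mechanism regressions are not a main problem. The change is worth making because it costs little and removes a bias of known direction.

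**What to change.** Divide step length and step width by the body-length measure already used for non-dimensional speed, taken at the same visit. Express cadence in non-dimensional form with that same length. Name the measure (height or leg length) once and use it throughout.

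Use the scaled values in the T0–T2 paired tests and, for consistency, in models 1 and 2. Show metres and steps per minute descriptively only.

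The cost is a line or two of analysis text. The length must be recorded at T2 as well as at T0, which non-dimensional speed already requires. Table 2 of the article ticks physical examination at T0 only and does not say which length is taken at T2, so the visit schedule should state it.

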#### Effect modifiers

As potential effect modifiers, the following outcome measures will be assessed: demographic variables, disease characteristics, personal and family characteristics, level of functional mobility and physical fitness (explained below).

##### Physical fitness

Physical fitness will be measured by means of an aerobic and anaerobic exercise test on a bicycle ergometer. The aerobic test will be performed according to the protocol described by Balemans et al.
[53] and aerobic fitness will be defined as oxygen uptake over the 30 seconds with the highest sustained load (VO2_peak_) [ml^-1^⋅kg^-1^⋅min^-^1]. Anaerobic power will be determined using the 20 seconds Wingate Anaerobic cycling Test (20s-WAnT), a sprint test against a constant breaking torque
[54]. Anaerobic fitness will be defined by the mean anaerobic power over 20 seconds (P20_mean_) [W⋅kg^-1^ and by the highest power output within the 20 seconds, the peak anaerobic power (P20_peak_) [W⋅kg^-1^. Measurement procedures, equipment and protocols for both tests will be as described by Balemans et al.
[53].

#### Other outcomes

Other study outcome measures will include 1) the patient’s personal treatment goals, measured with Goal Attainment Scaling (GAS), 2) treatment adherence, assessed with a motivation diary and with the @monitor
[55], 3) satisfaction with the FRO, as perceived by the patient and parents and 4) FRO stiffness, measured with BRUCE, which is a recently developed device for measuring mechanical AFO properties
[56].

### Statistical analysis

#### Subject population

Demographic variables and disease characteristics will be summarised using descriptive statistics. Furthermore, the means, medians, standard deviations and 95% confidence interval (CI) of primary and secondary outcome measures will be presented for all visits. In addition, correlations between parameters will be examined using correlation coefficients and graphical techniques.

#### Evaluation of FRO efficacy

Evaluation of the efficacy of a subject’s optimal FRO will be based on analyses of pre/post-intervention differences in primary and secondary outcome measures. The pre-intervention (control) condition will be for shoes only. Mean data for these measurements (assessed at T0) will be compared to follow-up measurements (T2_Kopt_), using paired sample t-tests.

To identify working mechanisms, multivariate linear regression analyses will be applied to investigate which of the changes in gait biomechanics are associated with changes in walking energy cost (model 1) and daily activity (model 2). First, a univariate regression analysis (ANOVA) will be performed to determine which factors are significantly associated with changes in the biomechanics of gait (p≤0.1), followed by the analysis of significant factors (p≤.05) in a multivariate regression analysis model.

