#### Sample size

The sample size will be based on a power analysis of the expected changes (i.e. T0 versus T2) in the primary outcome, walking energy cost [J^-1^⋅kg^-1^⋅m^1^. According to literature, walking energy cost in children with CP may be 30-50% higher than in healthy children
[10-12]. SCP children with GMFCS levels I, II and III show a mean net EC of 5.02 (±1.70) J^-1^⋅kg^-1^⋅m^1^[26]. A reduction of 25% in this value (≈1.26 J^-1^⋅kg^-1^⋅m^1^) is considered to be a clinically significant change
[25,26]. Assuming a power of 80% and a significance level of 0.05, detecting a clinically significant change will require a sample size of 29 children
[44]. Allowing for a dropout of approximately 10%, a sample size of 32 will be sufficient.

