#### Identifying prognostic factors

Multivariate regression analysis will also be applied to investigate to what extent child characteristics and FRO stiffness represent determinants for success of FRO treatment, defined as decreased walking energy cost (model 1), improvement in daily activity (model 2) and positive GAS scores (model 3). Initially, a univariate regression analysis (ANOVA) will be performed to determine which factors are significantly associated with FRO treatment outcomes (p≤0.1). Significant factors (p≤.05) will then be included in a multivariate regression model. Model analysis will include factors such as level of physical fitness, baseline disease characteristics, gait pattern, level of functional mobility, environmental factors and FRO characteristics.

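### The univariate screen for working mechanisms names the models' predictors (changes in gait biomechanics) as its outcome; the 0.1 and 0.05 thresholds also need to be reconciled

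*Protocol article*

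**What the plan says.** All references are to the protocol article, Statistical analysis.

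- **Evaluation of FRO efficacy, purpose of the models.** The regressions are to show "which of the changes in gait biomechanics are associated with changes in walking energy cost (model 1) and daily activity (model 2"). Gait changes are the explanatory variables; energy cost and daily activity are the outcomes.
- **Evaluation of FRO efficacy, first and second step.** The univariate analysis is done "to determine which factors are significantly associated with changes in the biomechanics of gait (p≤0.1), followed by the analysis of significant factors (p≤.05") in the multivariable model.
- **Identifying prognostic factors, first step.** The parallel analysis is done "to determine which factors are significantly associated with FRO treatment outcomes (p≤0.1").
- **Identifying prognostic factors, second step.** "Significant factors (p≤.05) will then be included in a multivariate regression model".

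Neither section says how many candidate factors there are, and the mechanism section does not define what a factor is.

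**The concern.** A univariate screen is meant to pick candidate predictors by their relation to the outcome of the model they will enter. The mechanism section puts the predictors in the outcome's place. An analyst who follows that sentence tests nothing against energy cost or daily activity until the multivariable step. By then a gait change that matters for energy cost may have been removed, and another kept for reasons unrelated to energy cost.

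The thresholds raise a second question. A factor is called significantly associated at 0.1, and the next step then takes significant factors at 0.05. If both are entry rules, a factor with p = 0.07 passes one and fails the other, and the choice between them could be made after the data are seen.

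The Background lists working mechanisms and predictors of success together as the second of two main goals. The regression in the mechanism section is the stated method for the first of these.

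**Working it through.** **1. Outcome of the screen, section by section**

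| Section | Outcome of the final models | Outcome named in the univariate screen | Match? |
|---|---|---|---|
| Evaluation of FRO efficacy | Change in energy cost; change in daily activity | Changes in gait biomechanics | No |
| Identifying prognostic factors | Energy cost, daily activity, GAS scores, as treatment success | FRO treatment outcomes | Yes |

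The mismatch does not depend on what "factors" means in the mechanism section. Whatever they are, the stated screen relates them to gait changes and to neither model outcome. No other section corrects this. It is a conflict between adjacent sentences, and no arithmetic is needed to establish it.

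**2. Number of children**

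The plan gives no figure for the regressions, so I use its sample size before dropout, 29. Sample size states "Assuming a power of 80% and a significance level of 0.05", an SD of 1.70 and a difference of 1.26. The two-sided normal formula for two means gives

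2 × [1.70 × (1.960 + 0.842) / 1.26]² = 28.6, rounded up to 29,

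and 29 × 1.1 = 31.9, rounded up to 32. Both stated figures reproduce. They serve here only as the n for the regressions.

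**3. What separates the two thresholds**

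For one continuous factor in simple regression, the smallest absolute correlation that reaches a two-sided p is |r| = t / √(n − 2 + t²), with t on n − 2 degrees of freedom.

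| n | p ≤ 0.1 | p ≤ 0.05 |
|---|---|---|
| 29 | 1.703 / √(27 + 1.703²) = 0.311 | 2.052 / √(27 + 2.052²) = 0.367 |
| 32 | 0.296 | 0.349 |

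At n = 29, a factor with |r| from 0.311 to just under 0.367 enters under one rule and not the other.

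The chance that a truly related factor enters, from 20,000 simulated samples of 29 (bivariate normal data, assumed true correlations):

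| True correlation | Enters at 0.1 | Enters at 0.05 |
|---|---|---|
| 0.3 | 48% | 36% |
| 0.4 | 71% | 60% |
| 0.5 | 89% | 81% |

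**4. False entry**

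The number of candidates, k, is not stated, so a range is assumed. For k independent candidates unrelated to the outcome, the chance that at least one enters is 1 − (1 − α)^k.

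| k (assumed) | α = 0.1 | α = 0.05 |
|---|---|---|
| 5 | 1 − 0.9⁵ = 41% | 1 − 0.95⁵ = 23% |
| 10 | 65% | 40% |
| 20 | 88% | 64% |

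Joint angles, moments and step parameters from the same gait trials will be correlated, which would lower these figures. They describe the threshold question only and do not measure the misnamed outcome.

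**The case against.** **It is probably a wording slip.** The sentence just before the screen states the models correctly, and the prognostic section gives the parallel screen in its proper form. Someone reading both would probably recover the intended direction. This stands as an account of how the error arose. It limits what can be claimed: a reader might infer that the mechanism analysis will in fact be run on the wrong outcome and have no bearing on energy cost or daily activity. The documents show only that one sentence says so, not that this analysis is intended. The sentence is still wrong as written, and nothing else in the article overrides it.

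**The thresholds may be an ordinary two-stage scheme.** In the mechanism section, 0.1 can be read as the screening level and 0.05 as the significance level within the multivariable model. On that reading a factor with p = 0.07 simply goes forward. This also stands. A reader might infer an outright contradiction in both sections, but the mechanism section is only ambiguous. The prognostic section is harder to read this way, because it makes 0.05 the condition for being included, directly after a 0.1 screen.

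**It is secondary.** The paired comparison of T0 with T2, the sample size and the choice of optimal FRO do not use these regressions. This is correct, and it sets the severity.

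**Conclusion.** The point holds for the misnamed outcome. The mechanism screen, as written, selects on the predictors of models 1 and 2 instead of on change in energy cost or change in daily activity.

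The threshold point holds as a secondary one: it is a conflict in the prognostic section and an ambiguity in the mechanism section. At n = 29 it affects factors with |r| between about 0.31 and 0.37. With 5 to 20 independent null candidates, an assumed range, at least one would enter in 41–88% of analyses at 0.1 and 23–64% at 0.05.

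The misnamed outcome touches the mechanism part of the second goal; the thresholds touch the predictor part as well. A reader might extend this to the whole second goal or to the main efficacy result. The text does not support that, because the prognostic screen names the right outcomes and the primary paired t-test is separate. This should be fixed, but it does not threaten the trial's main conclusion.

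**What to change.** 1. In Evaluation of FRO efficacy, name change in walking energy cost (model 1) and change in daily activity (model 2) as the dependent variable at both the univariate and the multivariable step. State that the candidate factors are the changes in gait biomechanics.
2. In both sections, state one univariate entry threshold. If 0.05 is meant as the significance or retention level within the multivariable model, say so separately.

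Replacing the screen with a short pre-named set of gait changes is a possible choice of method, but neither defect requires it.

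The cost is a few sentences of wording in the protocol or analysis plan. No change to data collection, sample size or the primary analysis is needed. The change should be made before the follow-up data are examined.
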